## Abstract

**Background:**

Hepatitis C (HCV) poses a major public health problem in the USA. While early identification is a critical priority, subsequent linkage to a treatment specialist is a crucial step that bridges diagnosed patients to treatment, cure, and prevention of ongoing transmission. Emergency departments (EDs) serve as an important clinical setting for HCV screening, although optimal methods of linkage-to-care for HCV-diagnosed individuals remain unknown. In this article, we describe the rationale and design of The *D*etermining *E*ffective *T*esting in *E*mergency Departments and *C*are Coordination on *T*reatment Outcomes (DETECT) for *Hep*atitis *C* (Hep C) Linkage-to-Care Trial.

**Methods:**

The DETECT Hep C Linkage-to-Care Trial will be a single-center prospective comparative effectiveness randomized two-arm parallel-group superiority trial to test the effectiveness of linkage navigation and clinician referral among ED patients identified with untreated HCV with a primary hypothesis that linkage navigation plus clinician referral is superior to clinician referral alone when using treatment initiation as the primary outcome. Participants will be enrolled in the ED at Denver Health Medical Center (Denver, CO), an urban, safety-net hospital with approximately 75,000 annual adult ED visits. This trial was designed to enroll a maximum of 280 HCV RNA-positive participants with one planned interim analysis based on methods by O’Brien and Fleming. This trial will further inform the evaluation of cost effectiveness, disparities, and social determinants of health in linkage-to-care, treatment, and disease progression.

**Discussion:**

When complete, the DETECT Hep C Linkage-to-Care Trial will significantly inform how best to perform linkage-to-care among ED patients identified with HCV.

**Trial registration:**

ClinicalTrials.gov

ID: NCT04026867

Original date: July 1, 2019

URL: https://clinicaltrials.gov/ct2/show/NCT04026867

**Supplementary Information:**

The online version contains supplementary material available at 10.1186/s13063-022-07018-w.

## Introduction

Hepatitis C (HCV) is associated with significant morbidity and mortality in the USA and abroad [1–3]. The World Health Organization set a goal of eliminating viral hepatitis as a public health threat by 2030 and lists increasing HCV treatment as a key target of the elimination strategy [4]. Despite the high burden of disease caused by HCV and the heightened global awareness of the problem, many people living with HCV remain undiagnosed and therefore untreated [5]. Efforts to offer testing more broadly and more often are a crucial first step for increasing treatment. To that end, emergency departments (EDs) have been identified as key settings in which to offer HCV testing to individuals who might not otherwise interact with healthcare systems or be offered HCV testing [6–10].

Once diagnosed, linkage-to-care is the next critical component of the HCV care continuum (Fig. 1). Effective linkage-to-care has been a major challenge for ED-based HCV testing with studies reporting linkage for only 20–39% of those newly diagnosed [11, 12]. However, unlike HCV, many HIV testing programs have successfully implemented active linkage programs, yielding successful linkage rates of well over 80% within 3 months of HIV diagnosis [13]. Linkage navigators have been utilized in community-based HCV testing programs, but while the role of navigation has been described in these settings, the added benefit of a linkage navigator above and beyond standard clinician referral has not been evaluated in a prospective, comparative manner [14–16]. Additionally, the effectiveness of navigators for people who inject drugs (PWID), a traditionally under-treated population, has not been assessed. Given that HCV is now curable with short courses of well-tolerated, increasingly available medications, the critical elements to slowing the epidemic are now HCV testing and effective linkage to care [17–19]. In high-volume ED settings, a linkage navigator may improve laboratory follow-up results disclosure, posttest counseling, linkage-to-care, and ultimately treatment and cure.

**Fig. 1 Fig1:**
[figure not shown]
Natural progression of hepatitis C virus (HCV) infection (**A**) and the HCV care continuum (**B**). SVR, sustained virologic response 12 weeks of completion of treatment

The overall objectives of the *D*etermining *E*ffective *T*esting in *E*mergency Departments and *C*are Coordination on *T*reatment Outcomes (DETECT) for *Hep*atitis *C* (Hep C) study are to (1) compare the effectiveness of two forms of HCV screening—non-risk-based (nontargeted) and risk-based (targeted) HCV screening (Screening Trial)— [20] (2) compare the effectiveness of two forms of referral to treatment for ED patients identified with HCV—linkage navigation plus clinician referral versus clinician referral alone (Linkage-to-Care Trial), (3) measure and compare programmatic costs and project long-term clinical outcomes, costs, and cost effectiveness of ED-based HCV screening and linkage-to-care (Cost Evaluation), and (4) examine the effects of disparities and social determinants of health on linkage-to-care, treatment initiation, and treatment completion among patients identified with HCV in the ED (Disparities and Social Determinants of Health Evaluation).

This article describes the rationale and design for the Linkage-to-Care Trial and is reported in accordance with the SPIRIT Statement for clinical trials [21, 22]. The primary hypothesis for the Linkage-to-Care Trial is that linkage navigation in addition to clinician referral will significantly increase the proportion of newly HCV-diagnosed individuals who complete care visits and initiate treatment when compared to clinician referral alone. The protocol (Version 3.3, Date February 17, 2022) is provided in the Additional.

## Methods

The DETECT Hep C Linkage-to-Care Trial has been registered in ClinicalTrials.gov and will be reported in accordance with CONSORT guidelines [23].

### Trial design

For this trial, we will perform a single-center prospective randomized two-arm parallel-group superiority trial to evaluate the effectiveness of two linkage-to-care strategies for patients newly identified with untreated HCV in the ED from the DETECT Hep C Screening Trial or through an active surveillance process of previously diagnosed patients (Fig. 2) [20]. Permuted block randomization with two strata (i.e., those less likely to initiate treatment: <40 years of age or active injection drug use (IDU) [defined as IDU within 30 days of enrollment] or those more likely to initiate treatment: ≥ 40 years of age and without active IDU) and varying block sizes will be used to minimize imbalance and to ensure appropriate numbers of patients in subgroups.

**Fig. 2 Fig2:**
[figure not shown]
Study schematic for the The DETECT Hep C Trials, including the emergency department (ED) screening trial (**A**) and the ED linkage-to-care trial (**B**) [blue circle with “R” = randomization; green circle with “S” = survey/satisfaction; pink rectangle = primary outcome; light pink rectangle = secondary outcomes]. HCV, hepatitis C; PWID, person who injects drugs

### Study setting

This study will be performed at Denver Health (Denver, CO), a nationally recognized anchor institution, safety-net hospital, and integrated health care system that includes an acute care hospital and level I trauma center, 9 federally qualified community health centers, multiple specialty clinics including hepatology and infectious diseases, and the Public Health Institute at Denver Health.

### Eligibility criteria

Patients eligible for this trial will include those who meet criteria for inclusion in the DETECT Hep C Screening Trial and who test positive for HCV antibodies and those seen in the ED with previously diagnosed untreated active HCV confirmed in the electronic health record (EHR). Exclusions will include the following: prisoners and individuals who live outside of Colorado (given follow-up constraints), patients who speak a language other than English or Spanish (as the interview for participants will only be available in English and Spanish), and those who are pregnant (because HCV treatment is not currently approved for pregnancy). Those who are randomized with positive HCV antibody tests but have subsequent undetected HCV RNA results will be excluded from the study.

### Interventions

This trial will consist of a comparative evaluation of two forms of linkage-to-care among ED patients identified with untreated HCV. The first intervention, *clinician referral*, will serve as an “active control” and reference standard of care. All individuals included in this arm will be informed of their HCV antibody result by the ED treating provider who will be prompted to confirm that standardized language is included in discharge instructions as part of an automated after visit summary process, including post-testing information and specific follow-up guidance. Patients will also be instructed to access their electronic patient portal for their RNA test results or to call a designated results line. Patients with untreated active HCV (i.e., previously detected HCV RNA with no subsequent undetected RNA in their medical record) will receive tailored discharge instructions specific for individuals identified as having previously diagnosed but untreated HCV.

The second intervention, *clinician referral plus linkage navigation*, will consist of an additional service layered onto clinician referral and will incorporate protocols from Antiretroviral Treatment and Access Studies (ARTAS), the most influential studies of HIV linkage-to-care to date [13, 24]. Individuals allocated to this intervention will be contacted by a linkage navigator either during the ED visit (if during business hours) or the following business day (if during non-business hours). If the navigator does not meet with the patient at the time of enrollment, he or she will offer to meet with the patient in person or over the phone when convenient for the patient. For all individuals in this arm, a structured linkage navigation process will include (1) reiteration of posttest counseling messages and (2) assessment of the patient’s needs for medical insurance and substance use disorder treatment referral; navigation will also include (3) referral to an appropriate HCV treatment specialist with assistance scheduling appointments, (4) coordination of appointments with an enrollment specialist, if needed, (5) provision of social services (e.g., provision of transportation vouchers and referral to health insurance enrollment assistance, HIV care, local harm reduction services, and mental health services), (6) coordination of appointment scheduling including rescheduling missed appointments through the entire HCV treatment process, and (7) contacting patients after appointments to assess their understanding and any additional needs regarding engagement in HCV care (see “Linkage-to-Care Manual” in the Additional file 1).

Linkage navigators will undergo structured training prior to the start of the trial and will provide follow-up services for up to 18 months from the time of enrollment with a minimum of three attempted contacts for patients who are difficult to reach. For individuals who test negative for HCV RNA, linkage navigators will make no more than three attempts to contact the patient to (1) deliver and explain the RNA results, (2) discuss the risk of reinfection and future testing recommendations, and (3) provide resources for insurance enrollment and substance use disorder treatment, as needed.

### Allocation

#### Sequence generation, allocation concealment, and implementation

Participants who meet criteria for inclusion will be stratified into two groups (i.e., < 40 years of age or IDU or ≥ 40 years and no IDU) then randomly assigned using variable block randomization for each stratum to one of the two study arms. Sequence of random assignments will be generated in SAS Enterprise Guide Version 7.1 (SAS Institute, Inc., Cary, NC) and transferred into REDCap (Vanderbilt University, Nashville, TN) for use with enrollment. Integration of the randomization sequences into REDCap will allow for concealed allocation as research assistants will not be able to anticipate allocation. As such, patients who consent for participation will be randomly assigned to one of the two study arms by a research assistant.

### Blinding

Participants and ED staff will understand the conceptual goals of the trial but will be blinded to the details of the study hypotheses. Outcomes will be determined using research staff blinded to study group allocation and hypotheses.

### Recruitment

Recruitment of participants will occur by trained research staff during dedicated recruitment hours that will vary from 7 a.m. through 10 p.m., 7 days a week. The research team will work to optimize research staff coverage to correspond with ED census but will also create mechanisms to remotely screen and enroll. This includes enrollment over the phone for patients who are eligible for the trial but have already left the ED. These patients may also choose to return to the medical campus for in person enrollment. Participants will receive a $25 gift card for participation in the study.

### Participant timeline

Primary research activities, including screening for participation, consenting, and randomization by research assistants will typically occur during the patient’s ED visit, with an option for remote enrollment after the visit as described above. Clinician referral and follow-up guidance are standard procedure for all patients in the ED with newly or previously diagnosed HCV. For those allocated to the linkage navigation arm, a linkage navigator will meet with the patient during the ED visit if during standard business hours, or, if not during business hours (e.g., evenings, nights, weekends, or holidays), will make contact by telephone the next business day to facilitate an appointment for subsequent care with an HCV treatment specialist.

### Outcomes

The *primary outcome* for this trial will be initiation of HCV treatment within 12 months from the time of enrollment for those with a positive HCV RNA test. *Secondary outcomes* will include the following: (a) linkage to an HCV treatment specialist within 12 months of enrollment; (b) for individuals who report IDU, initiation or continuation of substance use disorder services within 12 months of enrollment; (c) completion of a full course of HCV treatment with direct-acting antiviral medicines (DAAs) within 18 months of enrollment; (d) sustained virologic response 12 weeks (SVR12) as measured by report of a negative HCV RNA test at least 12 weeks after completion of DAAs [17]; and (e) all outcomes within 18 months of enrollment. Individuals without evidence of an HCV-associated visit within 18 months from ED diagnosis or ED visit will be considered not linked to care. All outcome measures will be collected and verified via EHR review by trained research assistants blinded to study allocation.

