### Sample size

The *primary superiority hypothesis* for this trial was powered based on a conservative estimate of HCV treatment initiation of 10% for clinician referral and a hypothesized increase to 30% (absolute increase of 20%) for those allocated to the linkage navigation intervention (Fig. 3). This trial was powered based on the < 40 years of age or IDU stratum to ensure adequate power overall. As such, it was estimated that a minimum of 140 participants (70 per arm) will be required in each stratum for a total of 280 participants to achieve a power of 80%, using an alpha of 0.0492 based on methods for one interim analysis by O’Brien and Fleming. Using the approach by O’Brien-Fleming, the interim analysis will occur at the study’s halfway point, after 140 total patients (approximately 35 per arm) have been enrolled and outcomes data collected, and with an effectiveness threshold of *p* < 0.0054 for the primary outcome. A non-binding futility threshold of *p* > 0.5 will be used for the primary outcome. If the trial is not stopped after the interim analysis, it will proceed to enroll the full sample (280) with a significance effectiveness threshold of *p* < 0.0492.

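### Secondary outcome (b) pools starting substance use disorder services with continuing services already in place, which dilutes the contrast between arms and blurs what it would mean

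*Protocol article*

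**What the plan says.** In the protocol article, Outcomes, secondary outcome (b) reads: "for individuals who report IDU, initiation or continuation of substance use disorder services within 12 months of enrollment". Item (e) of the same list adds "all outcomes within 18 months of enrollment", so (b) is assessed again at 18 months. On data source the section states: "All outcome measures will be collected and verified via EHR review by trained research assistants blinded to study allocation".

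Under Interventions, the navigator's substance-use task is "assessment of the patient’s needs for medical insurance and substance use disorder treatment referral". The navigator also provides social services such as transportation vouchers and referrals to harm reduction and mental health services, and follows participants for up to 18 months.

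Under Trial design, the stratification variable is "active injection drug use (IDU) [defined as IDU within 30 days of enrollment". The allocation section then abbreviates the strata to "< 40 years of age or IDU or ≥ 40 years and no IDU", and Sample size likewise uses the bare term for the same stratum.

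**The concern.** The outcome joins two events that apply to different people. Only someone outside services at enrollment can initiate, and only someone already in services can continue. The needs assessment and referral act mainly on the first group. The second group can succeed in either arm for reasons unrelated to navigation, and those successes add equally to both rates while adding nothing to the difference.

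Two things are at stake. A real effect on entry to services may be missed. And whatever difference is found cannot be assigned to entry or to retention, which are different claims about what a navigator achieves. The Introduction says that the effectiveness of navigators for people who inject drugs has not been assessed, and (b) is the only listed outcome specific to that group.

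**Working it through.** **The plan's own figure.** The only sample-size figure is for the primary outcome. It rests on "a conservative estimate of HCV treatment initiation of 10% for clinician referral and a hypothesized increase to 30% (absolute increase of 20" and gives "a minimum of 140 participants (70 per arm) will be required in each stratum for a total of 280 participants", at alpha 0.0492 and 80% power. A two-sided comparison of 10% with 30% needs 62 per arm without continuity correction and 72 with it. At 70 per arm, power is 84.7% for the uncorrected chi-square test and 81.3% for Fisher's exact test. The stated 70 is therefore sound, and this point does not touch it.

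**Inputs for (b).** The article gives none, so all of the following are assumed:
- 50 IDU participants per arm;
- initiation r = 15% (referral) vs 35% (navigation) among those not in services;
- a share q of each arm already in services, of whom a proportion c continues.

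**Formulas.** The arm rate is p = q·c + (1 − q)·r. If c is equal in both arms, the difference is (1 − q)(r₂ − r₁). Approximate power is Φ(|p₂ − p₁|/SE − 1.96), with SE = √{[p₁(1 − p₁) + p₂(1 − p₂)]/n}.

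**Case A: all baseline users continue in both arms (c = 1).** For q = 0.4:
- p₁ = 0.40 + 0.60 × 0.15 = 0.49 and p₂ = 0.40 + 0.60 × 0.35 = 0.61;
- SE = √[(0.2499 + 0.2379)/50] = 0.0988;
- 0.12/0.0988 − 1.96 = −0.745, so power is about 23%.

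Restricting to those not in services leaves n = 30 per arm at 15% vs 35%:
- SE = √[(0.1275 + 0.2275)/30] = 0.1088;
- 0.20/0.1088 − 1.96 = −0.12, so power is about 45%.

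| q | Combined rates | Difference | Power, combined | Power, restricted |
|---|---|---|---|---|
| 20% | 32% vs 48% | 16 points | 38% | 56% |
| 40% | 49% vs 61% | 12 points | 23% | 45% |
| 50% | 57.5% vs 67.5% | 10 points | 18% | 39% |

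**Case B: some drop out equally (c = 80% in both arms).** The differences are again 16, 12 and 10 points, with power 39%, 23% and 17%. The dilution does not need every baseline user to succeed.

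**Case C: navigation also improves retention (c = 55% vs 75%, q = 0.4).**
- p₁ = 0.4 × 0.55 + 0.6 × 0.15 = 0.31 and p₂ = 0.4 × 0.75 + 0.6 × 0.35 = 0.51;
- SE = √[(0.2139 + 0.2499)/50] = 0.0963;
- 0.20/0.0963 − 1.96 = 0.117, so power is about 55%.

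Here the combined outcome does better than the restricted one (45%).

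**Stratified test on the combined outcome.** In simulations with 50 per arm and q = 0.4, a test stratified on service status at enrollment had about 44% power against 24% for the pooled test when all baseline users continue. In Case C it had 61% against 55%. It was ahead of the pooled test in every scenario tried.

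**Sensitivity to the assumptions.** With 10% vs 30% among those able to start, 70 per arm, two-sided alpha 0.05, and 10% to 40% already in services and counted as successes, the 20-point difference falls to between 18 and 12 points. Power falls from about 85% to between 66% and 29%.

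**The case against.** Retention in services is a legitimate goal. A navigator who arranges transport and social services and follows participants for up to 18 months could plausibly affect it. Case C shows that dropping continuation could then cost power. This stands, and it is why the combined outcome should not simply be replaced by initiation alone.

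The article also condenses a full protocol (Version 3.3) that is not shown. What counts as a service, and what evidence shows continuation, may be defined there, so their absence here is no fault. But such definitions would not separate the two events, and pooling them is what the article itself fixes.

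Two stronger readings are tempting and lack support:
- **Success at enrollment.** A reader might infer that participants already in services succeed automatically. The text asks for continuation within 12 months, which may require recorded service use after enrollment, and a baseline user can drop out and fail.
- **Former injectors in the denominator.** A reader might infer that anyone who ever injected is included and that long-past injectors count as failures in both arms. The article does not say so. Elsewhere it uses bare IDU for the 30-day active-IDU stratum, and a former injector still in services could qualify through continuation. The recency window needs a wording clarification only.

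**Conclusion.** The point holds for the pooling of initiation with continuation. It affects one secondary outcome, at 12 and 18 months. The consequence is dilution and unclear interpretation. It is not bias, since service use at enrollment is balanced between arms in expectation.

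The size is illustrative. If continuation is equal in both arms, the difference shrinks in proportion to the share already in services. If navigation improves retention as well, the difference may not shrink at all. In both situations a single combined rate leaves open whether navigation changed entry, retention or both.

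**What to change.** Keep the combined outcome as written and add three things:

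1. Record from the EHR whether each IDU participant was in substance use disorder services at enrollment. Use only entries dated before enrollment, abstracted by the same blinded staff.
2. Compare arms on the combined outcome with a test stratified on that status, such as Cochran-Mantel-Haenszel.
3. Report initiation among those not in services at enrollment separately from continuation among those already in services.

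In the outcome wording, also state whether reporting IDU means the 30-day definition used for stratification.

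The cost is one baseline EHR field and smaller denominators, hence wider intervals, for each component. Enrollment began in November 2019 and the interim analysis took place on August 1, 2022. The additions should therefore be written down before the final comparison of (b) and dated as later specifications. Keeping the combined outcome means that nothing already declared is withdrawn.
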